## Abstract

**Background:**

Older adults who are frail face significant barriers to physical activity, and innovative solutions such as synchronous telerehabilitation (STR) may provide a viable alternative to traditional face-to-face programs. However, less is known about its effectiveness compared to a face-to-face program.

**Objective:**

This study aims to compare the effectiveness of an STR program versus a face-to-face physical therapy (FPT) program in the primary outcomes (lower body strength and cardiorespiratory fitness) and secondary outcomes (upper limb strength, dynamic balance, static balance, number of steps, functional status, and quality of life) in older adults who are frail.

**Methods:**

In a randomized, blinded, parallel-group controlled trial, all older adults who are frail and aged ≥60 years of both sexes from the Los Angeles Comprehensive Center for Older Adults will be invited to participate. A total of 58 older adults who are frail (aged ≥60 years) meeting the eligibility criteria will be randomly assigned to either an STR group (n=29, 50%) or an FPT group (n=29, 50%). Participants will engage in 1-hour multicomponent exercise sessions twice weekly for 12 weeks. The telerehabilitation group will participate via videoconferencing, supervised remotely by technical staff, while the face-to-face group will attend in-person sessions. Outcomes will include lower limb strength (sit-to-stand test), cardiorespiratory fitness (2-minute step test), upper limb strength (grip strength test), balance (Timed Up and Go, and single-leg stance), quality of life (36-item brief health survey), functional status (functional independence measure), and daily steps (pedometer).

**Results:**

Recruitment will be conducted from April to May 2025. The intervention will run from June to August 2025, follow-up assessments will be completed by September 2025, and data analysis will be finalized by December 2025. Manuscript drafting and submission are planned for March 2026. We hypothesize that STR will yield equal or superior improvements in both primary and secondary outcomes compared to FPT in older adults who are frail.

**Conclusions:**

STR is emerging as a viable and effective alternative to in-person physical therapy for older adults with frailty. This approach has the potential to improve physical condition and functional and quality of life indicators, overcoming geographical and logistical barriers and optimizing therapeutic resources.

**Trial Registration:**

ClinicalTrials.gov NCT06784245; https://clinicaltrials.gov/study/NCT06784245

**International Registered Report Identifier (IRRID):**

PRR1-10.2196/72318

## Introduction

### Background

Worldwide, the prevalence of frailty in people aged ≥60 years ranges from 7% to 24% [1]. In Latin America and the Caribbean, the prevalence of frailty ranges from 7% to 42.6% [2]. A recent study conducted in Chile found that 10.9% of individuals aged >60 years are frail, including 7.7% of men and 14.1% of women affected. The study also reported that the prevalence of frailty in Chile increases significantly with age, reaching 58% for men and 62% for women after the age of 80 years [3]. Frailty is a clinical stage with a multifactorial etiology that involves disorders of multiple interconnected physiological systems [4]. Its diagnosis is commonly based on 5 components: muscle strength, gait, exhaustion, weight loss, and chronic fatigue [5]. People who are frail have a higher risk of falls, disability, long-term care, and death [6]. Therefore, prevention and early detection have become significant challenges for public health and clinical practice [7].

The first-line therapy for managing frailty should include a multicomponent physical activity program with a resistance-based training component [8]. Recent evidence shows the efficacy of a multicomponent exercise program as a strategy to prevent [9] and reverse frailty to prefrailty. In addition, it has been seen that a multicomponent exercise program can improve physical fitness, particularly resistance and balance [10,11], and quality of life [12] in older adults with this clinical stage. Despite the many benefits of exercise, participation is low among older adults, with relatively few older adults who are frail meeting the recommendations for exercise [13,14].

In Chile, the “More Autovalent Older Adults” (*Más Adulto Mayor Autovalente)* program, implemented by the Ministry of Health, is one of the primary national strategies aimed at promoting and maintaining functionality and physical fitness in older adults [15]. International and national experience indicates that most of these programs are group-based aerobic exercises and the promotion of self-care. Furthermore, participation rates may fluctuate due to factors such as time, available space, weather conditions [16,17], or distance between home and the exercise location, representing a barrier for older adults to join or maintain their attendance at out-of-home programs [18]. As a result, older adults are more likely to develop sarcopenia or frailty due to the decrease in physical activity [19]. In addition, exercise instructors have a more difficult time offering individual instruction to their older adult participants when the physical activity program is carried out with large groups and heterogeneous health characteristics and may have trouble providing effective feedback relevant to their cognitive characteristics [19]. Home-based exercise alternatives have been proposed to overcome the limitations of conventional programs, such as videos, online platforms, and mobile apps [20]. However, this modality does not offer direct feedback, making it difficult for older adults to benefit fully, and the risk of injury is higher [19].

In this context, telerehabilitation has been proposed as a new intervention method to prevent or improve frailty. Telerehabilitation refers to the delivery of rehabilitation services to patients remotely, using information and communication technologies [21]. Communication between the patient and the rehabilitation professional may occur through a variety of technologies, such as the telephone and internet‐based videoconferencing [22]. Widely accepted advantages exist for the use of telerehabilitation rather than the more traditional, clinic-based service delivery model. Telerehabilitation facilitates access to rehabilitation opportunities [23], reduces health care disparities, and allows patients to receive services in the comfort and privacy of their own homes [24,25]. This model eliminates geographical barriers [26-28] and reduces both the time and out-of-pocket expenses associated with transportation. In addition, it diminishes the reliance on others for mobility or the need for adapted transportation for some older individuals who are frail [24,27,29,30]. Consequently, telerehabilitation is associated with increased session attendance and functional improvements comparable to or even superior to those achieved with in-person care [31].

Synchronous telerehabilitation (STR) involves real-time, two-way video and audio communication between the exercise instructor and participant, allowing for supervised training using high-speed telecommunications technologies. This would allow for real-time interactions between exercise instructors and older adults living in their homes [32,33]. Three international studies have evaluated the effectiveness of STR programs for older adults at high risk of falls and sarcopenia. Significant improvements were found in physical condition (leg strength measured with the chair stand test), static balance (Berg Balance Scale), and decreased sarcopenia [19,33,34]. Telerehabilitation is considered a viable alternative to traditional rehabilitation, as it reduces the use of outpatient resources and improves quality of life. However, further randomized controlled trials are required to evaluate its efficacy in older adults with chronic diseases, frailty, and sarcopenia [35-37].

To date, few studies in Chile have reported using these mobile technologies (asynchronous telerehabilitation) to support the treatment of older adults on physical fitness and functional status [38]. Nonetheless, no studies have been found examining the effects of an STR program on the physical capacity, functional status, and quality of life of older people who are frail. Few studies have rigorously examined whether patients achieve comparable benefits from in-clinic versus remote physiotherapy telerehabilitation sessions. Much of the existing research implements a hybrid model of combined home and clinic sessions rather than just remote delivery [39]. This is because the combined service delivery increases confidence in the accuracy of diagnosis and assessment of progress by providing regular opportunities for physical contact and manipulation of a patient’s extremities and joints. Regardless of whether a combined or remote-only model is used, studies comparing telerehabilitation with clinic-based physiotherapy consistently suggest that both approaches yield comparable results [39,40].

### Objectives

In this context, this study aims to analyze whether the effectiveness of an STR program is better than a face-to-face physical therapy (FPT) program in the primary outcomes (lower body strength and cardiorespiratory fitness) and secondary outcomes (upper limb strength, dynamic balance, static balance, number of steps, functional status, and quality of life) in older adults who are frail. We hypothesize that (1) both STR and FPT programs improve primary (lower body strength and cardiorespiratory fitness) and secondary outcomes (upper limb strength, dynamic balance, static balance, number of steps, functional status, and quality of life) in older adults who are frail and (2) STR produces equal or greater improvements compared to face-to-face programs in these outcomes.

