### Randomization

The sample will be selected by quota until a size of 58 participants is reached. The selection will be random among those who meet the inclusion and exclusion criteria. Participants will be randomized by research staff using a computer-generated sequence and concealed allocation to one of the following two groups: (1) the STR group, which will receive STR, or (2) the FPT group, which will receive FPT. A simple randomization computational sequence stratified by gender, age, and frailty will be used to obtain a balance between men and women, age ranges, and severity of frailty in both groups. The randomization sequence will be concealed using sequentially numbered, opaque, sealed envelopes to ensure allocation concealment (Figure 1).

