**Figure 2 figure2:**
[figure not shown]
Study design of the synchronous telerehabilitation intervention program.

In addition, at that time, STR group participants will be provided with a tablet and home exercise equipment (exercise mats, resistance bands, cones, and dumbbells). If exercise materials are lost or damaged, they will be replaced. A home visit will be conducted to identify barriers to exercise and assess the most suitable location to carry out the STR sessions. One week before the intervention, there will be 2 induction sessions on the proper use of sports equipment, as well as video calls. Written and verbal instructions will be provided outlining the simple steps necessary to connect to an online meeting and facilitate participation in the STR program, as well as the proper use of the home exercise equipment. In addition to the induction sessions, asynchronous material was provided to address questions related to connectivity and the use of devices such as tablets and watches.

At the beginning of the interventions, all participants will be given a hydration kit (cotton towel and a water bottle) and a smartwatch (Fitbit Inspire 2, Google LLC) to measure continuous heart rate monitoring during exercise sessions to maintain exercise intensity, and pedometer (OMRON HJ-321, Kyoto, Japan) to record the number of daily steps each participant takes. (All the equipment that will be delivered to participants is guaranteed).

During the intervention period, nutrition guidance and exercise education will be provided to all participants once every 4 weeks. Throughout the 12-week intervention period, the participants will be encouraged to maintain the same physical activity levels and calorie intake as before participating in the study. During the education sessions, we will inform the participants to inform the support personnel holding the education sessions about any changes in physical activity levels or nutrition intake. A record will be kept of the number of sessions completed by each participant, which will serve as an indicator of adherence to the program. In addition to session attendance, retention rates (including reasons for nonattendance or withdrawal) and interactions with the technical support team will be recorded.

A postintervention assessment will be conducted after the last week of the 12-week program (Figure 2).

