### Interventions

#### Overview

Regardless of the group (STR or FPT), each session will consist of a warm-up activity (5-10 minutes), main exercise activity (30-40 minutes), and cool-down activity (5-10 minutes) following the guidelines of a multicomponent exercise program, Vivifrail [46]. Exercise intensity will be controlled based on the Rating of Perceived Exertion (RPE) [47] on the Borg scale [48] and heart rate measured with a smartwatch [49] before, during, and after each exercise session according to the guidelines of the American College of Sports Medicine [47]. The warm-up and cool-down activities will include stretching and walking in place (9≤RPE≤10 and 40<55% maximum heart rate (HRmax), while the main exercise activity will consist of strength, resistance exercise, cardiovascular exercises, and balance exercises (to prevent falls) performed using dumbbells, color-coded resistance bands (Thera-Band; Hygienic Corp) [50] and a chair (11<RPE≤15 and 55<70 HRmax).

To ensure safety and compliance, exercise training will be supervised by a health professional (physical therapist) who has been appropriately trained (research support staff). This health professional will provide one-on-one instructions to each participant according to the target RPE and HRmax (measured with a smartwatch) for each session. All participants will interact with the same health professionals.

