### Outcome Measures

#### Overview

Physical fitness, functional status, and quality of life will be examined before and after the interventions. All measurements will be performed by a health professional (technical staff will be trained), blinded to the group allocation scheme, which will guarantee an unbiased procedure. In addition, all measurements will be conducted in a face-to-face setting and obtained individually in an environment with optimal conditions of privacy, temperature, and humidity, such as an older care center collaborating with the project. Data will be recorded on standardized forms and entered into a secure access database that contains quality control checks (eg, range checks and notifications for missing data). The main outcome for this trial will be lower body strength (assessed in the 30-second chair stand test) and cardiorespiratory fitness (evaluated using the 2-minute step test). Secondary outcomes included upper limb strength, dynamic balance, static balance, number of daily steps, functional status, and quality of life.

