### Statistical Analysis

Missing data will be handled by intention-to-treat analysis (multiple imputation method) [67]. The description will be made as measures of central tendency and dispersion (continuous variables) and as percentages (categorical variables). Using the Shapiro-Wilk test, the normality of the data will be verified, and a two-step approach for transforming will be applied to the nonnormal variables [68]. Homoscedasticity will be analyzed using Levene test. A 2-way repeated measures ANOVA will be used to determine the effects of interventions. The effects of the model are the group (experimental group vs control group), the time points (before and after test), and their interaction over time (time × group). The Bonferroni post hoc test will be applied to identify statistically significant comparisons. The *t* test effect size will be determined using Cohen *d* (<0.2 insignificant; ≥0.2 and ≤0.49 small; ≥0.5 and ≤0.79 moderate; ≥0.8 large) [69]. All analyses will be performed using SPSS (version 26; IBM Corp), with a significance level of *P*<.05, and GraphPad Prism (version 8).

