## Discussion

### Anticipated Findings

It is plausible that both an STR program and a face-to-face physiotherapy program have positive effects on the primary and secondary outcomes of the study. This hypothesis is based on evidence from systematic reviews and meta-analyses that supports how exercise-based interventions generate benefits in muscle strength, balance, cardiorespiratory fitness, quality of life, and the number of daily steps in older people [35,38,70,71].

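### Hypothesis 1, that both programmes improve the outcomes, cannot be tested by this design: with no untreated arm, before-after change cannot be attributed to the programmes

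*Protocol article*

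**What the plan says.** The Objectives section states two hypotheses. The first is that "both STR and FPT programs improve primary (lower body strength and cardiorespiratory fitness) and secondary outcomes". The second is that "STR produces equal or greater improvements compared to face-to-face programs in these outcomes".

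Under Randomization there are two arms: "1) the STR group, which will receive STR, or (2) the FPT group, which will receive FPT". Under Interventions, Overview, the session content is common to both: "Regardless of the group (STR or FPT), each session will consist of a warm-up activity (5-10 minutes), main exercise activity (30-40 minutes". Under Procedure, "nutrition guidance and exercise education will be provided to all participants once every 4 weeks".

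Under Outcome Measures, Overview, "Physical fitness, functional status, and quality of life will be examined before and after the interventions". No repeated baseline or run-in is described.

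The Statistical Analysis section presents a two-way repeated measures ANOVA as the means of establishing what the interventions do. Its terms are group, "the time points (before and after test), and their interaction over time (time × group"). A Bonferroni post hoc step follows, and the comparisons it covers are not named. The Anticipated Findings section considers it plausible that both programmes "have positive effects on the primary and secondary outcomes of the study".

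**The concern.** To say that a programme improves an outcome is a causal statement about that programme, and hypothesis 1 makes it for each arm separately. The group and time × group terms compare the arms with each other, so they cannot answer it. That leaves the time effect or a before-after contrast within an arm, and neither is a randomised comparison.

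The protocol itself shows three other reasons why scores could rise:

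- **Practice.** Several outcomes are performance tests done twice: sit-to-stand, 2-minute step, grip, Timed Up and Go and single-leg stance.
- **Regression to the mean.** Participants are enrolled because they meet a frailty phenotype. The Background lists muscle strength and gait among its usual components.
- **Shared education.** Nutrition guidance and exercise education go to both arms.

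At stake is whether the report may say that each programme is effective. A significant time effect would look like support for that statement, although it could arise with no programme effect at all.

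**Working it through.** **1. Which term answers which hypothesis**

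| Model term | What it compares | Randomised? | Hypothesis served |
|---|---|---|---|
| Group | Arms, averaged over both visits | Yes | Neither directly |
| Time, or change within an arm | After with before | No | 1 |
| Time × group | Change in STR with change in FPT | Yes | 2 |

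**2. The plan's own sample size**

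Inputs from Power Calculation: α 0.05, power 0.80, effect size 0.8. A two-sided two-sample t test with 26 per arm has noncentrality 0.8 × √(26/2) = 2.884 on 50 degrees of freedom, and power 0.807. With 25 per arm the power is 0.791, so 26 per arm, 52 in total, reproduces. Adding 6 gives 58. The figure is sound for a difference between two arms. It does not bear on hypothesis 1.

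**3. Chance of a significant improvement when the programmes do nothing**

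The documents give neither the non-programme gain g (in baseline SDs) nor the pre-post correlation r. Both are assumed here, over g = 0.1 to 0.4 and r = 0.5 to 0.8.

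Standardised change: dz = g / √(2(1 − r)). The noncentrality is dz × √n, where n is 52 for the pooled time effect (50 degrees of freedom) and 26 for one arm (25 degrees of freedom). Tests are two-sided at 0.05, counting significance in the favourable direction only.

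Example, g = 0.3 and r = 0.7:
- dz = 0.3 / √0.6 = 0.387.
- Time effect: noncentrality 0.387 × √52 = 2.79, critical t 2.009, probability 0.782.
- One arm: noncentrality 0.387 × √26 = 1.97, critical t 2.060, probability 0.476.

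Probability of a significant time effect, 52 completers:

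| g | r = 0.5 | r = 0.7 | r = 0.8 |
|---|---|---|---|
| 0.1 | 0.105 | 0.148 | 0.200 |
| 0.2 | 0.293 | 0.447 | 0.609 |
| 0.3 | 0.564 | 0.782 | 0.918 |
| 0.4 | 0.807 | 0.955 | 0.994 |

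With g = 0 the rate is the nominal 0.025 in this direction.

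**4. If the hypothesis is tested within each arm**

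Hypothesis 1 says both programmes improve. The arms are independent, so on one outcome at g = 0.3 and r = 0.7:
- Uncorrected: 0.476² = 0.23.
- Bonferroni for two arms (α 0.025 each): one arm 0.357, both arms 0.357² = 0.13.

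**5. The randomised comparison under the same shift**

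A gain shared by both arms cancels in the difference of changes, so the time × group test keeps its level. A simulation of 20,000 trials (29 per arm, g = 0.3, r = 0.8) gave 4.8% against the nominal 5%.

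**The case against.** The strongest reply is that the trial is comparative. The stated aim is STR against FPT, the sample size is for two groups, and shared practice, regression and education cancel in the randomised contrast. This stands in full: hypothesis 2 is untouched.

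Second, no sentence says that a significant time effect will be credited to the programmes, or that the post hoc tests are within-arm. A reader might infer both, because no other term can serve hypothesis 1 and the ANOVA is offered as showing intervention effects. It remains an inference, and the point does not need it: whichever before-after contrast is used, it cannot carry the causal claim.

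Third, a reader might infer that the article already concludes effectiveness from before-after change. The text does not support that. Anticipated Findings speaks of plausibility and rests on outside reviews, the closing Conclusions are conditional, and the abstract's conclusion was written before any data. Reading a non-significant interaction as equality of the programmes is a separate matter and adds no weight here.

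Fourth, the rival explanations are partly tempered. Participants are asked to keep their usual activity and calorie intake and to report changes. The frailty components overlap only indirectly with the two primary tests, and the article does not say whether screening values serve as baseline. These points may shrink the non-programme gain. They do not let the design measure it or rule it out.

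Finally, the probabilities depend on assumptions, and a single figure such as 78% for the time effect would overstate what is known. Hence the range, and the lower figures for both arms.

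**Conclusion.** The point holds for hypothesis 1 only. With two active arms, one assessment before and one after, and no untreated comparator, neither the time effect nor a within-arm contrast can attribute change to the programmes. That conclusion is structural and does not depend on the assumed values.

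Its practical size does. If the programmes had no effect, the time effect would be significant in anything from about 11% to 99% of trials across the assumed range with 52 completers. At 0.3 SD and a correlation of 0.7, both arms would be significant in about 23% of trials, or 13% after Bonferroni for two arms, on one outcome. The documents contain nothing that narrows this range.

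The Strengths and Limitations section does not mention the missing comparator, practice or regression to the mean. The sample size and the randomised STR-FPT comparison are not called into question.

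**What to change.** - **Objectives:** restate hypothesis 1 as a descriptive objective. Report the mean change in each arm with a 95% confidence interval, and do not use it as a test of effectiveness.
- **Statistical Analysis:** state that intervention effects are judged only on the between-arm difference, either time × group or the baseline-adjusted difference after treatment.
- **Conclusions:** limit claims to STR relative to FPT. The conditional wording need not be struck out, provided it is not later supported by before-after change.
- **Strengths and Limitations:** name the lack of an untreated comparator, with practice, regression to the mean and the shared education as unseparated explanations.

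No arm, participant or visit is added; the cost is wording. The downside is that the trial gives up the claim that each programme is effective on its own.

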### Power Calculation

The sample size was calculated a priori using G*Power 3.1.9.7. A total of 52 participants in total are required (26 in each group), considering Cronbach α=.05, 1-β=.8, and effect size=0.8 (lower limb strength based on the results of a previous study) [19]. Considering the possibility of abandonment, 6 participants were added (N=58; n=29 in each group; Figure 1 [42]).

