### Conclusions

Implementing STR programs could represent a viable and effective alternative to in-person physical therapy for older adults who are frail. This innovative approach would not only achieve comparable or superior improvements in strength, cardiorespiratory fitness, and other functional indicators but also facilitate access to rehabilitation by overcoming geographical and logistical barriers. Telerehabilitation would allow for the personalization and optimization of therapeutic resources, improving the quality of life and independence of a vulnerable population. These potential findings would have important implications for integrating remote strategies into routine practice and for fostering future research that expands their application in clinical settings.

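### The plan hypothesises that STR is equal to or better than FPT, but its sample size and only test address a difference, so the equality half of the hypothesis cannot be established

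*Protocol article*

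**What the plan says.** All references are to the protocol article.

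- **Objectives, aim:** the study will "analyze whether the effectiveness of an STR program is better than a face-to-face physical therapy (FPT) program".
- **Objectives, second hypothesis (same paragraph):** "STR produces equal or greater improvements compared to face-to-face programs in these outcomes".
- **Abstract, Results:** "We hypothesize that STR will yield equal or superior improvements in both primary and secondary outcomes compared to FPT".
- **Strengths and Limitations:** the authors again expect results at least as good as those of the face-to-face programme.
- **Conclusions:** STR "would not only achieve comparable or superior improvements in strength" and other indicators.
- **Power Calculation:** 26 per group, 52 in total, "considering Cronbach α=.05, 1-β=.8, and effect size=0.8 (lower limb strength based on the results of a previous study". Six are added for dropout, giving 58. Sidedness is not stated.
- **Statistical Analysis:** "A 2-way repeated measures ANOVA will be used to determine the effects of interventions". The model has group, time and time × group terms, Bonferroni post hoc tests, Cohen d with descriptive bands, and significance at P<.05.

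The article states no non-inferiority or equivalence margin, and no rule based on a confidence interval.

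**The concern.** *Better* and *equal or greater* are different statistical questions. The first is tested against a null of no difference. The second is a non-inferiority claim: its null is that STR is worse by at least a stated amount, so it cannot be tested until that amount is fixed. The article asks both questions in one paragraph and provides machinery only for the first.

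This is not detail left to an unseen analysis plan. The hypothesis, the sample size and the test are all stated here, and they do not fit each other.

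Both arms follow the same multicomponent programme with the same intensity targets and the same health professionals (Interventions, Overview), so a small between-arm difference is plausible. The Conclusions say the findings would bear on integrating remote delivery into routine practice. A non-significant result from a trial of this size could leave a moderate STR deficit open, while the hypothesis as worded invites the reader to count it as a success.

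**Working it through.** **1. Reproduce the plan's sample size.** Inputs from Power Calculation: d = 0.8, α = 0.05, power 0.80. For a two-sample t test with n per arm, df = 2n − 2 and the noncentrality is d·√(n/2).

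- Two-sided: n = 26 gives power 0.807 and n = 25 gives 0.791, so 26 per arm are needed. This matches the plan.
- One-sided: 21 per arm would suffice. This does not match.

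The arithmetic is correct, and the plan's figure is that of a two-sided difference test.

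**2. Put the planned test on its own scale.** With two time points, the time × group F test is a t test on change scores. If the SD is the same at both times and the pre-post correlation is ρ, the SD of change is SD·√(2(1 − ρ)). The article gives no ρ, so 0.5 to 0.8 is an assumption:

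- ρ = 0.5: √1.0 = 1.00 SD
- ρ = 0.7: √0.6 = 0.775 SD
- ρ = 0.8: √0.4 = 0.632 SD

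A true deficit of Δ SD has standardised size Δ/√(2(1 − ρ)). For example, 0.5 SD at ρ = 0.8 is 0.5/0.632 = 0.791, with noncentrality 0.791·√13 = 2.85.

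**3. Probability of a non-significant result when STR is truly worse** (two-sided 5%, noncentral t):

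| True deficit | ρ | 26 per arm | 29 per arm |
|---|---|---|---|
| 0.3 SD | 0.5 | 81% | 80% |
| 0.3 SD | 0.7 | 72% | 69% |
| 0.3 SD | 0.8 | 61% | 57% |
| 0.5 SD | 0.5 | 58% | 54% |
| 0.5 SD | 0.7 | 37% | 32% |
| 0.5 SD | 0.8 | 20% | 16% |

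The lower boundary of the plan's own *moderate* band for Cohen d is 0.5.

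**4. Precision.** The 95% CI half-width for the difference in change is t(.975, 50)·√(2/26)·√(2(1 − ρ)), and t(.975, 50)·√(2/26) = 2.009 × 0.277 = 0.557.

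- ρ = 0.5: 0.56 SD
- ρ = 0.7: 0.557 × 0.775 = 0.43 SD
- ρ = 0.8: 0.557 × 0.632 = 0.35 SD

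**5. What margin could this size support?** Assume a true difference of zero, one-sided α of 0.025 and 80% power. On the unit-SD scale the margin is 0.792 SD with 26 per arm. Multiplying by √(2(1 − ρ)) gives 0.79 SD at ρ = 0.5, 0.792 × 0.775 = 0.61 SD at ρ = 0.7, and 0.792 × 0.632 = 0.50 SD at ρ = 0.8.

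Conversely, by normal approximation, n per arm = 2(1.960 + 0.842)²·2(1 − ρ)/margin²:

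| Margin (assumed) | ρ = 0.5 | ρ = 0.7 | ρ = 0.8 |
|---|---|---|---|
| 0.5 SD | 63 | 38 | 26 |
| 0.3 SD | 175 | 105 | 70 |

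**The case against.** **The plan can be read as a coherent superiority trial.** The stated aim, the sizing and the interaction test all agree on superiority, and nothing labels the trial as non-inferiority. The wording on equality appears as a hypothesis, an expectation or a conditional conclusion. This stands in part: it shows that the machinery needs no redesign if the claim is limited to superiority. It does not remove the mismatch, because the hypothesis is formally stated and half of it has no test.

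**A reader might infer that the authors will report P≥.05 as equality.** The article does not say so. That would be a prediction about future reporting, not a stated rule. What the article supports is narrower: it hypothesises equality and offers no valid way to conclude it.

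**The P value is not the only output.** Cohen d is also planned, with values below 0.2 called insignificant. That is correct, so non-significance is not the only thing a reader would see. But a point estimate without an interval or a margin does not rule out a deficit, so the gap remains.

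**The size depends on unstated inputs.** The 81% and 58% figures apply to the planned test only if ρ is 0.5, and quoting them alone would overstate the problem. At ρ = 0.8 a deficit of 0.5 SD is missed in only about 20% of trials. It is also an assumption that the arms will differ little, since the plan itself assumes 0.8. The range must be shown. A 0.3 SD deficit, however, is missed more often than not across the whole range, even with all 29 per arm.

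**Conclusion.** The concern holds as a mismatch between hypothesis and method. The Objectives section states a superiority aim and an equal-or-greater hypothesis. The sample size and analysis serve the first only, and nothing in the plan can validly establish the second. The sample-size arithmetic itself is right.

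With 26 per arm, and across the assumed correlations of 0.5 to 0.8, the time × group test would be non-significant in about 81% to 61% of trials if STR were worse by 0.3 SD, and in about 58% to 20% if worse by 0.5 SD. With 29 per arm the ranges are 80% to 57% and 54% to 16%. These figures rest on normal outcomes, equal SDs at both times, and deficit sizes chosen for illustration. The absence of a valid route to equality does not depend on them.

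**What to change.** Make the aim and hypothesis in Objectives agree. Either route below does this.

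**Minimum repair: superiority only.** Delete the claims of equality or comparability from the Abstract (Results), Objectives, Strengths and Limitations, and Conclusions. For each primary outcome, report the baseline-adjusted STR minus FPT difference with its two-sided 95% CI. State that P≥.05 is not evidence of equality. This costs wording and one added estimate per outcome, with no extra participants and no change to the sample size.

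**If equal or greater is kept:**

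1. Reconcile the lower-limb strength outcome. Outcome Measures (Overview) names a 30-second chair stand, while Primary Outcomes describes a timed 5-repetition test. Benefit runs in opposite directions on the two, so no margin in the test's own units can be written until one is fixed.
2. Prespecify and justify a margin for each of the two primary outcomes, and say whether both must be met.
3. Judge non-inferiority on the 95% CI, test superiority afterwards, and call anything else inconclusive. Within one outcome this order needs no alpha adjustment.
4. State that, on change scores with 26 per arm and true equality, 80% power exists only for margins from about 0.79 SD (correlation 0.5) down to about 0.50 SD (correlation 0.8). A tighter margin needs a larger trial or an explicit statement that the comparison is underpowered.

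This route costs two margin justifications and possibly more participants. The downside is that the trial may have to report an inconclusive result where it would otherwise have claimed equality.
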